## Abstract

**Background:**

Although there have been well-validated patient-reported outcome (PRO) measurements in dermatology practice, there is limited evidence of the adopted comprehensive aspects of PRO measures in long-term follow-up among people living with chronic pruritus. As such, we aim to create a cohort study of the Patient-Reported Outcomes among people living with Chronic Pruritus (PROs-CP) in Thailand.

**Methods and design:**

This study is a single-center, prospective, open cohort, observational longitudinal study using a multistage, mixed-methods parallel designs to integrate both quantitative and qualitative data regarding PROs among people living with chronic pruritus (itch lasting six or more weeks). The multistage of the PROs-CP study will comprise three sub-studies: (i) study I, PROs measure development, translation, and psychometric validation; (ii) study II, perspectives of people living with chronic pruritus to gain more information regarding disease burden and unmet treatment care responses; and (iii) study III, a longitudinal study to assess the impact of chronic pruritus on long-term health outcomes. Based on a comprehensive review of a panel of stakeholders with chronic skin disease, a set of PRO measurement tools will comprise an established validated Thai version. Meanwhile, meaningful non-Thai versions or unestablished PRO instruments will be translated and developed through this study as appropriate. Quantitative data will be collected based on PRO measures regarding pruritus symptoms and severity, disease activity control and treatment satisfaction, general- and dermatology-specific health-related quality of life, mental health and psychosocial issues, and psychosomatic symptoms. Qualitative data will be obtained from the patient’s perspectives through individual interviews.

**Ethics and dissemination:**

The study protocol was approved by the Ethics Committee of the Faculty of Medicine, Chiang Mai University (MED-2566-0299), Thailand. Our findings will be disseminated through scientific conferences and publications in peer-reviewed journals.

**Conclusion:**

Regarding the mixed-methods approach, this open cohort, prospective longitudinal study will provide an evidence-based better understanding of patient perspectives on chronic pruritus burden and inform the utility of a comprehensive set of PROs to measure their long-term health outcomes.

**Trial registration:**

Thai Clinical Trials Registry (TCTR, thaiclinicaltrials.org) registration TCTR20240327001 (registered on March 27, 2024).

## Introduction

Chronic pruritus is a common symptom in dermatology, characterized by the International Forum for the Study of Itch (IFSI) as present for more than six weeks [1, 2]. The point prevalence of chronic pruritus has been estimated to be more than one-third of patients in dermatology practice [3], and the lifetime prevalence rate ranges from 19.5% to 25.5% in the general population [4–6]. Chronic pruritus has substantial negative consequences on everyday life and deterioration of patients’ health-related quality of life (HRQoL) [7–10]. Specifically, chronic pruritus is the major factor in relation to impairing the HRQoL and health outcomes among patients with chronic inflammatory skin diseases, systemic diseases, and idiopathic/rare diseases [7, 8, 10–13]. Furthermore, chronic pruritus has not only immense negative strains on HRQoL but also significantly impairs physical function and mental health issues, including healthcare utilization [8, 13, 14].

Unfortunately, there is no international consensus for objectively measuring tools to capture the severity and associated symptoms burden of pruritus in practice. To date, subjective symptoms experiences measured based on patient-reported remains the best available practical approach for quantifying disease burden, which accounts for and reflects the patient’s view. However, apart from the clinical outcomes assessment, overarching aspects of chronic pruritus on a patient’s life are underrecognized and poorly understood. Indeed, comprehensive sets of validated patient-reported outcome (PRO) measures are needed in dermatological practice to help identify and track responses to disease management treatments, clinically meaningful improvements, and support as a part of treatment decision-making. To close the gap and harmonize pruritus outcome measures, adopting standardized specific PROs that directly capture perspectives of patients living with chronic pruritus in daily practice will facilitate better treatment comparison and outcomes reporting.

To the best of our knowledge, although there have been well-validated PRO measurement tools in dermatology research [10, 15–23], there is limited evidence of the adopted comprehensive aspects of PRO measures in long-term follow-up among people living with chronic pruritus. In this regard, we aim to create the PROs-CP (Patient-Reported Outcomes among people living with Chronic Pruritus), a single-center, open cohort, observational longitudinal study in Thailand. We will employ a multistage, mixed-methods approach to incorporate both qualitative and quantitative information from patient perspectives to better understand pruritus burden and associated symptoms and track treatment responses among Thai patients with chronic pruritus.

## Objectives

### Primary objectives

To establish and validate the psychometric properties regarding validity, reliability, and responsiveness of the comprehensive sets of PROs-CP measures for Thai patients with chronic pruritus.To explore the patient perspectives on living with chronic pruritus and the burden of pruritus severity and symptoms.To assess the impact of chronic pruritus on long-term PROs-CP, including HRQoL, symptoms burden, mental health, psychosocial issues, and psychosomatic symptoms.

### Secondary objectives

To define a minimal clinically important difference (MCID) of the particular PROs-CP measure for clinically meaningful interpretation among Thai patients with chronic pruritus.To investigate the health utility and economic burden of Thai patients with chronic pruritus, including healthcare expenditures and out-of-pocket costs.

## Material and methods

### Patient and public involvement

Chronic pruritus patients will participate in the pilot testing and refinement of the questionnaire and provide feedback on the long-term acceptability of using the PROs-CP tools in daily practice. However, no patients or members of the public had a role in the study design, conceptualizing of the study, conducting the research, or reporting and dissemination plans.

### Study setting and design

This study is a single-center, prospective, observational longitudinal study at dermatology/general medicine clinics (public), Maharaj Nakorn Chiang Mai Hospital, Faculty of Medicine, Chiang Mai University, Thailand. The PROs-CP cohort will be conducted using mixed-methods parallel designs, integrating quantitative and qualitative data [24]. Based on a multi-methodical (Fig 1), the multistage of the PROs-CP study will comprise three sub-studies, including study I, PROs measure development, translation, and psychometric validation; study II, explore the perspective of people living with chronic pruritus to gain more information regarding disease burden and unmet treatment care responses; and study III, a longitudinal study to assess the impact of chronic pruritus on long-term health outcomes (i.e., PROs, clinical outcomes and treatment responses, and health utilization and economic burden). Regarding the mixed-methods approach, this complex study process will provide an evidence-based better understanding of patient perspectives on chronic pruritus burden and inform the utility of a comprehensive set of PROs to measure their long-term health outcomes. This study was registered with the Thai Clinical Trials Registry (thaiclinicaltrials.org; TCTR20240327001, March 27, 2024).

**Fig 1 pone.0314548.g001:**
[figure not shown]
Component of sub-studies and process of the PROs-CP cohort. Abbreviations: PROs, patient-reported outcomes; PROs-CP, Patients-Reported Outcomes among People Living with Chronic Pruritus.

### Study population

Based on routine clinical practice and to create an open or dynamic cohort, all adult patients with chronic pruritus, regardless of the IFSI classification to skin manifestation (i.e., inflamed skin, non-inflamed skin, and chronic secondary scratch lesions) in outpatient settings, will be consecutively recruited for this study project. Chronic pruritus patients will be diagnosed based on the recommendation of the IFSI—defined as pruritus lasting six or more weeks [1, 2]. Details of the eligible patients for the study are provided in Table 1.

**Table 1 pone.0314548.t001:** Eligibility criteria of the PROs-CP study.

Inclusion Criteria	Exclusion Criteria
• Patients aged ≥20 years at the date of screening • Diagnosed with chronic pruritus based on the IFSI recommendation, itch lasting more than 6 weeks [1, 2] • Could read and communicate in the Thai language • Had an ability to understand and willingness to sign an informed consent statement and adhere to the study protocol	• Inability to answer questions or comply with the study protocol due to both physical and mental disability • Recent hospitalization within 3 months • The prognosis for survival <12 months

Abbreviations: IFSI, International Forum for the Study of Itch; PROs-CP, Patients-Reported Outcomes among People Living with Chronic Pruritus.

### Study PROs measure instrument

The preliminary sets of PRO measures for patients with chronic pruritus were carefully reviewed based on comprehensive literature reviews and a panel of stakeholders with chronic skin, including dermatologists and experts in dermatology research (SN, CR, SK, RR, PC, NT, SC, and MC), health policy expert (KT) and patient’s perspectives. Moreover, experts in qualitative research (RA, CP, and YR) in conjunction with a third-party expert in linguistics were also reviewed in terms of relevancy, readability, and applicability in the PROs measure to be included in the study. In this circumstance, most of the instruments in the aspects of pruritus symptoms and severity, general- and dermatology-specific HRQoL, mental health, psychosocial, and psychosomatic symptoms are validated and available in the Thai version, which is ready to implement in the study III. However, three validated non-Thai version instruments, namely—ItchyQoL (pruritus-specific HRQoL) [18, 25], Patient Unique Stigmatization Holistic tool in Dermatology (PUSH-D) [16], and Toronto Alexithymia Scale 20-item (TAS-20) [26, 27], which require to translate and testing for psychometric properties in this study. Moreover, we also identified unavailable and unestablished particular instruments for chronic pruritus regarding the domains of disease activity control and treatment satisfaction. Thus, we will develop and validate these instruments by conducting Study I. The PRO-CPs instruments ready to be used and planned to be translated and developed are described in Table 2.

**Table 2 pone.0314548.t002:** Measurement tools for the PROs-CP study.

Instrument	Established Measures	Available in the Thai Version	Description
**Aspect of Pruritus**			
Pruritus intensity—VAS	Yes	Yes	• A VAS-10 cm was used to measure the degree of pruritus intensity [12, 19]. • The recall period was determined to be 24 h, both the worst and average pruritus intensity.
Pruritus intensity—VRS	Yes	Yes	• A VRS based on a 5-point Likert scale was used to measure the degree of pruritus intensity [12, 19]. • The recall period was determined to be 24 h, both the worst and average pruritus intensity.
Pruritus intensity—NRS	Yes	Yes	• An NRS of 0 to 10 points was used to measure the degree of pruritus intensity [12, 19]. • The recall period was determined to be 24 h, both the worst and average pruritus intensity.
5-D itch	Yes	Yes	• The 5-D itch scale consists of 8 items in 5 domains and evaluates itch symptoms. • This scale revealed acceptable psychometric properties, with a Cronbach’s α of 0.75 among pruritic dermatoses in Thailand [17].
Patient’s global assessment of pruritus control	No: developed through this study	Yes: psychometric testing through this study	• A single-item NRS of 0–10 points was used to measure the degree of pruritus activity control.
Global rating of change in pruritus symptom	No: developed through this study	Yes: psychometric testing through this study	• A single-item NRS of -7 (a very great deal worse) to 7 (a very great deal better) points was used to measure the degree of change in pruritus symptom over the past 4-week. If participants indicated that there had been no change, they were given a score of zero.
Chronic pruritus—multidimensional scale for disease control	No: developed through this study	Yes: psychometric testing through this study	• Planned to develop and initial validate a multidimensional scale for assessing disease activity control among patients with chronic pruritus.
Satisfaction with treatment care	No: developed through this study	Yes: psychometric testing through this study	• A single-item NRS of 0–10 points was used to measure global satisfaction with treatment care.
Treatment satisfaction-multidimensional scale for chronic pruritus	No: developed through this study	Yes: psychometric testing through this study	• Planned to develop and initial validate a multidimensional scale for capturing treatment satisfaction among patients with chronic pruritus.
**Aspect of HRQoL**			
DLQI	Yes	Yes	• The DLQI comprises a 10-item dermatology-specific HRQoL instrument (total score ranges from 0 to 30) [23]. • Internationally, this scale had acceptable to excellent psychometric properties, with Cronbach’s α ranges of 0.75 to 0.92 [22]. • For banding of the score, DLQI was categorized into 0–1 (no effect), 2–5 (small effect), 6–10 (moderate effect), 11–20 (very large effect), and 21–30 (extremely large effect) [22].
EQ-5D-5L	Yes	Yes	• The EQ-5D-5L measures health state utility values, 5-level assessment of mobility, self-care, usual activities, pain/discomfort, anxiety/depression, and the VAS of health state [44].
Self-rated health—WHO	Yes	Yes	• A single item is used to measure QOL based on a 5-point Likert scale of self-rated health [45].
ItchyQoL	Yes	No: translated and psychometric testing through this study	• The validity and reliability have been established on a satisfactory scale in individuals with chronic pruritus [18, 21, 25]. • The internal consistency and test-retest reliability (stability) with Cronbach’s α reliability and intraclass correlation coefficient ranges from 0.89 to 0.99 and 0.84 to 0.98, respectively [18, 25]. • For scale interpretation, ItchyQoL scores were classified as follows: 0–30 (little), 31–50 (mild), 51–80 (moderate), and 81–110 (severe) [20].
Global rating of change in HRQoL scale	Yes	Yes	• A single-item NRS of -7 (a very great deal worse) to 7 (a very great deal better) points was used to measure the degree of change in HRQoL. If participants indicated that there had been no change, they were given a score of zero [46].
**Aspect of mental health, psychosocial, and psychosomatic symptoms**			
PHQ-9	Yes	Yes	• The PHQ-9 consists of 9 items to measure depressive symptoms (total score ranges from 0 to 27). • This scale showed excellent psychometric properties, with a Cronbach’s α of 0.90 among the general population in Thailand [29, 47]. • A cut-off point ≥9 was considered to indicate depressive symptoms [48].
GAD-7	Yes	Yes	• The GAD-7 consists of 7 items to measure anxiety symptoms (total score ranges from 0 to 21). • This scale had excellent psychometric properties, with a Cronbach’s α of 0.90 among the general population in Thailand [29, 47]. • A cut-off point ≥8 was considered to indicate depressive symptoms [49].
WHO-5 well-being index	Yes	Yes	• The WHO-5 well-being index consists of 5 items to measure health-related personal well-being. • This scale had excellent psychometric properties, with a Cronbach’s α of 0.91 among the general population in Thailand [29, 47]. • A cut-off point <50 was considered a low well-being index [47].
BRCS	Yes	Yes	• The BRCS consists of 4 items to measure cope tendencies with psychological stress (total score ranges from 4 to 20). • This scale had excellent psychometric properties, with a Cronbach’s α of 0.84 among the general population in Thailand [29].
TAS-20	Yes	No: translated and psychometric testing through this study	• The TAS-20 consists of 20 items to measure alexithymia (difficulty in identifying and describing emotions) [27]. • The non-Thai version showed adequate psychometric properties in 30 different languages (or dialects of the same language) [26].
PUSH-D	Yes	No: translated and psychometric testing through this study	• The PUSH-D is a dermatologic-specific scale to evaluate stigmatization in patients with visible skin conditions, which consists of 17 items [16]. • This scale demonstrated excellent psychometric properties, with Cronbach’s α 0.94 [16].
RSES	Yes	Yes	• The RSES consists of 10 items to measure self-esteem and is widely used in social science research. • The revised Thai RSES scale demonstrated excellent psychometric properties, with Cronbach’s α ranging from 0.84 to 0.86 [50].
UCLA Loneliness Scale-6	Yes	Yes	• The short version of the UCLA loneliness scale consists of 6 items to gauge loneliness levels. • This scale revealed acceptable psychometric properties in both non-clinical and clinical settings, with Cronbach’s α ranging from 0.72 to 0.84 [51].
ISI-7	Yes	Yes	• The ISI-7 consists of 7 items to assess the nature, severity, and impact of insomnia (total score ranges from 0 to 28). • This scale showed good psychometric properties, with a Cronbach’s α of 0.84 among the general population in Thailand [29, 47]. • A cut-off point ≥12 was considered to indicate insomnia symptoms [52].
SSS-8	Yes	Yes	• The SSS-8 consists of 8 items to measure somatic symptom burden (total score ranges from 0 to 32) [53]. • This scale showed good psychometric properties, with a Cronbach’s α of 0.84 among the general population in Thailand [29, 47]. • The SSS-8 severity categories were categorized as follows: 0–3 points (no to minimal), 4–7 points (low), 8–11 points (medium), 12–15 points (high), and 16–32 points (very high) [53].
Global Sleep problems—NRS	No: developed through this study	Yes: psychometric testing through this study	• A single-item NRS of 0–10 points was used to measure the global degree of sleep problems.
Global Fatigue—NRS	Yes	Yes	• A single-item NRS of 0 to 10 points was used to measure the global degree of fatigue [54]. The recall period was determined during the past 7 days.
Pain intensity—NRS	Yes	Yes	• A single-item NRS of 0 to 10 points was used to measure the degree of pain intensity [55]. • The recall period was determined to be 24 h, both the worst and average paint intensity.
MAST	Yes	Yes	• The MAST consists of 8 items to measure medication adherence. • This scale had good psychometric properties, with a Cronbach’s α of 0.83 among chronic disease patients in Thailand [56].

Abbreviations: BRCS, Brief Resilient Coping Scale; DLQI, Dermatological Life Quality Index; EQ-5D-5L, EuroQoL-5 dimension-5 level; GAD-7, Generalized Anxiety Disorder 7-item; HRQoL, health-related quality of life; ISI, Insomnia Severity Index 7-item; MAST, Medication adherence using the Medication Adherence Scale in Thais; NA, not applicable; NRS, numerical rating scale; PHQ-9, Patient Health Questionnaire 9-item; PROs-CP, Patients-Reported Outcomes among People Living with Chronic Pruritus; PUSH-D, Patient Unique Stigmatization Holistic tool in Dermatology; RSES, Rosenberg Self-Esteem Scale; SSS-8, Somatic Symptom Scale 8-item; TAS-20, Toronto Alexithymia Scale 20-item; UCLA, University of California, Los Angeles; VAS, visual analogue scale; VRS, verbal rating scale; WHO, World Health Organization.

### Study I: PROs measure development, translation, and psychometric validation

We will follow the established methods and consecutive phases for scale development to create multidimensional scales [8, 28]. The series of phases for scale development are illustrated in Fig 2. In brief, phase I—item generation will review the literature regarding general- and pruritus-specific disease activity control and treatment satisfaction. The subsample of 30 patients with chronic pruritus will be interviewed using structured and non-structured in-depth interviews to provide and reflect the perspectives regarding pruritus-specific disease control and their satisfaction with treatment care. In phase II, we will generate pilot questionnaires based on literature review and patient perspectives. The pilot questionnaires will then be reviewed by a panel of experts and patients to modify and verify in terms of face and content validity. In phase III, we will refine the particular questionnaire via an optimal sample to establish scale dimensionality using exploratory factor analysis (EFA, based on the rule of thumbs, 5–15 patients per question) and non-parametric item response theory (IRT) [8, 28, 29]. Lastly, in phase IV, we will perform an initial psychometric analysis to verify the validity and reliability of the final scale. For scale stability, a random subsample will be asked to complete the particular scale twice, within a 60–120 min interval.

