Two independent bilingual native English speakers will independently blind-translate the synthesized measurement scales back into English. For the back-translation process, no translators had any medical health/dermatology background or acknowledged information regarding the particular original English version. To ensure that the translated version reflects the content of the original version, the content validity of the back-translation questionnaire will be reviewed and addressed. After that, both versions of the backward translations will be compared and reconciled with the original English version. To ensure equivalence between the original and translated Thai versions, conceptual equivalence (ensuring that words can hold the same conceptual meaning), item equivalence (individual items have the same relevance), and semantic equivalence (meaning of the items is the same in both version) will be employed. In the same manner as pilot testing and refinement of the scale development, a panel of experts and patients will review and refine the preliminary translated scales. Next, the EFA, non-parametric IRT, and initially psychometric analysis will be conducted to establish the validity, reliability, and scale stability (reproducibility) of the translated scales Thai version (i.e., ItchyQoL, PUSH-D, and TAS-20).

To track the treatment responses, the responsiveness of the pruritus-specific disease activity control (planned to develop through this study) and pruritus-specific HRQoL (using the ItchyQoL) in terms of the MCID will also be defined and established among patients with chronic pruritus. For scale interpretability in terms of MCID, we will incorporate both anchor-based and distributional criterion approaches using the change scales of disease activity and ItchyQoL at week 12 of follow-up [31–33].

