To assess the psychometric properties, we will test the convergent validity of the sets of PROs-CP measurement scales using Pearson’s or Spearman’s correlation coefficients as appropriate. The 95% confidence intervals (CIs) of correlation coefficient statistics will be estimated using the bootstrap resampling method. A know-group or discriminant validity will be assessed based on pruritus intensity—visual analog scale as follows: mild (0.1–2.9), moderate (3.0–6.9), severe (7.0–8.9), and very severe (9.0–10.0) [2]. Internal consistency reliability will be tested using Cronbach’s α and McDonald’s ω coefficients with 95% CIs (values of >0.7 indicate acceptable reliability). Scale reproducibility will be tested using intraclass correlation coefficients. The kappa (κ) coefficient of the agreement and area under the receiver operating characteristic curve will be used to assess the optimal cut-off severity or burden score to establish banding of measurement scales with anchor-based questions.

All interviews’ audio recordings will be transcribed verbatim. Deidentified transcript data from the in-depth interview process will be uploaded, coded, and refined by professional experts in qualitative research (RA, CP, and YR). For qualitative analysis, we will employ content analysis to summarize the interview information and assess the consistency of coding and refinement concepts that capture patient views and experiences of chronic pruritus. A thematic approach based on grounded theory techniques will be used to analyze and identify patterns or themes (subthemes) from patient perspective information [35, 36]. Furthermore, we also plan to qualitatively synthesize among subgroups with severe or very severe pruritus intensity to reflect the impacts of chronic pruritus that are most important to patients with high-burden disease activity. The saturation of concept findings from qualitative interviews will be reaffirmed using saturation tables to verify and track the concepts of how pruritus affected the patient’s life.

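### Test-retest stability is measured over 60–120 minutes, so the reproducibility ICC is biased upward and describes short-term repeatability rather than stability

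*Protocol article*

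**What the plan says.** The interval is fixed in the protocol article, Study I, at the end of the description of the scale-development phases: for stability, a random subsample is to "complete the particular scale twice, within a 60–120 min interval". The Statistical analysis plan section adds the estimator: "Scale reproducibility will be tested using intraclass correlation coefficients".

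The same Study I section, in its account of the translated instruments, also plans stability testing for the Thai ItchyQoL, PUSH-D and TAS-20. It gives no separate interval for them, so the 60–120 minutes applies to them by implication only.

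For the new disease-control scale and ItchyQoL an MCID is planned: "we will incorporate both anchor-based and distributional criterion approaches using the change scales of disease activity and ItchyQoL at week 12 of follow-up". The distributional criterion is not named.

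The article gives no reason for the short interval. It describes no safeguard against recall, such as reordered items or a parallel form. Reliability is to be analysed again after six months and one year, but no new retest is set out there.

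**The concern.** A test-retest ICC is informative when the error in the second answer is independent of the error in the first. One to two hours later, many patients can reproduce what they ticked. Influences that differ from day to day, such as mood, sleep or the circumstances of completion, are largely the same on both occasions. Whatever error is shared in this way is counted as agreement between true scores, so the ICC rises for a reason unrelated to the quality of the scale.

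Reliability is part of the first primary objective, and Study III uses these instruments at visits 2–3 months apart. A figure obtained within two hours does not show how far a score moves between visits in a patient who has not changed. If the same ICC feeds a measurement-error criterion for meaningful change, that criterion is too small as well.

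**Working it through.** The plan states no target ICC, SEM or retest sample size, so it has no figure of its own to reproduce. The check asks which way shared error moves the ICC, and by how much under stated assumptions.

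**Inputs**
- Retest gap: 60–120 minutes (Study I).
- Illustrative true ICC: 0.84, the lower end of the published ItchyQoL range of 0.84–0.98 in Table 2. Values of 0.70 and 0.90 are added as assumptions.
- Carry-over ρ, the correlation between the answer errors on the two occasions: not in the documents. Assumed 0, 0.25, 0.50 and 0.75.

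**Formulae** (classical test theory, SEM and SDC in units of the score SD)
- Observed ICC = ICC + ρ × (1 − ICC)
- SEM = √(1 − observed ICC)
- Smallest detectable change, SDC = 1.96 × √2 × SEM
- Ratio of the SEM with carry-over to the SEM without = √(1 − ρ)

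**Results for a true ICC of 0.84**

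| ρ | Observed ICC | SEM | SDC | SEM too small by |
|---|---|---|---|---|
| 0 | 0.84 | √0.16 = 0.400 | 1.11 | 0% |
| 0.25 | 0.84 + 0.25 × 0.16 = 0.88 | √0.12 = 0.346 | 0.96 | 13% |
| 0.50 | 0.84 + 0.50 × 0.16 = 0.92 | √0.08 = 0.283 | 0.78 | 29% |
| 0.75 | 0.84 + 0.75 × 0.16 = 0.96 | √0.04 = 0.200 | 0.55 | 50% |

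A simulation of 200,000 pairs gave ICCs of 0.840, 0.880, 0.920 and 0.960 and SEMs of 0.399, 0.346, 0.283 and 0.200 SD, in agreement with the formulae.

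**Other starting values.** With ρ = 0.50, a true ICC of 0.70 is observed as 0.70 + 0.50 × 0.30 = 0.85, and a true ICC of 0.90 as 0.90 + 0.50 × 0.10 = 0.95. The proportional loss in the SEM depends only on ρ, so 13%, 29% and 50% hold whatever the true ICC. The ICC itself is inflated most where the scale is weakest.

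**The case against.** The best defence of a short gap is that itch may fluctuate and that these patients are under treatment. A retest days later can mix real change with measurement error and pull the ICC down. That is a fair reason not to wait long. It does not justify one to two hours, because real change can be handled by restricting the analysis to unchanged patients, whereas recall cannot be removed afterwards.

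The defence is also right that the consequences are limited. Several stronger conclusions are tempting, and the documents do not support them:

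- *The MCID will be too small.* The article does not name its distributional criterion. A fraction of an SD, or an SEM taken from Cronbach's α (which is planned), would not use the retest ICC. The anchor-based part does not use it either.
- *Reliability as a whole is overstated.* Only the retest ICC is affected. Cronbach's α, McDonald's ω, factor structure and the validity analyses do not depend on it.
- *The SEM is 2.8 times too small.* This comes from giving the short interval the top of the quoted ItchyQoL range and a longer interval the bottom: √0.16 / √0.02 = 2.8. The article does not report the retest intervals behind those values, and the step would need a carry-over of 0.14 / 0.16 = 0.875.
- *The recall windows of the two completions overlap by 92–96%.* This is 22/24 to 23/24 for a 24-hour window. Table 2 states a 24-hour window only for the itch and pain intensity scales, which are already established in Thai and are not the scales being retested.
- *Both completions take place at one clinic attendance.* The interval makes this likely, but the article does not say so.

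**Conclusion.** The point holds in a limited form. The plan's only described retest is too short to support a claim of stability, and the bias in its ICC is upward. The direction follows from the design, provided some error is shared over one to two hours. The size rests on the assumed carry-over, which the documents do not give. The 60–120 minute gap is stated directly for the newly developed scales, including the disease-control scale that is to receive an MCID, and is only implied for ItchyQoL, PUSH-D and TAS-20. The MCID consequence is conditional on an SEM or SDC built on this ICC. This should be fixed, but it does not undermine the psychometric programme as a whole.

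**What to change.** - Move the stability retest to a gap of days, for example about 7 with a window of 3–14. These values are a working convention and do not come from the documents.
- Keep the same mode of administration where possible. Otherwise collect the retest remotely and record the mode. Phone, text and email contact already exists for visit reminders.
- Take the primary ICC from patients who report no change since the first completion and had no treatment change in between. Use a question worded for that interval, because the study's own pruritus change rating looks back 4 weeks.
- Name the distributional criterion for the MCID. If it uses an SEM or SDC, base it on this ICC.
- State the retest interval for ItchyQoL, PUSH-D and TAS-20 explicitly.
- Report the 60–120 minute repeat, if kept, as supplementary short-term repeatability.

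The cost is a change of wording and one rescheduled questionnaire for a subsample that is already planned. The downsides are some non-return, loss of patients whose itch or treatment changed, and a possible mode effect that could itself lower the ICC. The timing is favourable. At 30 October 2024 the new scales were still in item generation, and their retest belongs to the last development phase. The three translated scales were already translated, so any retest begun on them would need a further subsample at the longer gap.
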